## Abstract

**Background:**

Electronic cigarettes (e-cigarettes or electronic nicotine delivery systems [ENDS]) are electrically powered devices generally similar in appearance to a cigarette that deliver a propylene glycol and/or glycerol mist to the airway of users when drawing on the mouthpiece. Nicotine and other substances such as flavourings may be included in the fluid vaporised by the device. People report using e-cigarettes to help quit smoking and studies of their effects on tobacco withdrawal and craving suggest good potential as smoking cessation aids. However, to date there have been no adequately powered randomised trials investigating their cessation efficacy or safety. This paper outlines the protocol for this study.

**Methods/design:**

*Design:* Parallel group, 3-arm, randomised controlled trial. *Participants:* People aged ≥18 years resident in Auckland, New Zealand (NZ) who want to quit smoking. *Intervention:* Stratified blocked randomisation to allocate participants to either Elusion™ e-cigarettes with nicotine cartridges (16 mg) or with placebo cartridges (i.e. no nicotine), or to nicotine patch (21 mg) alone. Participants randomised to the e-cigarette groups will be told to use them *ad libitum* for one week before and 12 weeks after quit day, while participants randomised to patches will be told to use them daily for the same period. All participants will be offered behavioural support to quit from the NZ Quitline. *Primary* o*utcome:* Biochemically verified (exhaled carbon monoxide) continuous abstinence at six months after quit day. *Sample size:* 657 people (292 in both the nicotine e-cigarette and nicotine patch groups and 73 in the placebo e-cigarettes group) will provide 80% power at *p* = 0.05 to detect an absolute difference of 10% in abstinence between the nicotine e-cigarette and nicotine patch groups, and 15% between the nicotine and placebo e-cigarette groups.

**Discussion:**

This trial will inform international debate and policy on the regulation and availability of e-cigarettes. If shown to be efficacious and safe, these devices could help many smokers as an alternative smoking cessation aid to standard nicotine products.

**Trial registration:**

Australian NZ Clinical Trials Registry (ACTRN12610000866000).

## Background

Most smokers want to quit and make attempts to do so but the majority of these attempts fail largely because of their dependence on nicotine and non-nicotine sensory and behavioural cues that reinforce their smoking behaviour [1]. Psychological and pharmacological smoking cessation treatments help smokers quit and are one of the most cost-effective health interventions available [2]. Indeed, nicotine replacement therapy (NRT) almost doubles quit rates irrespective of the level of additional behavioural support [3]. Nevertheless, absolute long-term quit rates with NRT are low: typically, fewer than 20% of people quitting with NRT plus behavioural support are still abstinent at 12 months [3]. Even the most rapid-acting and highest strength NRT products do not deliver nicotine in doses or at the same speed as cigarettes [4]. With the possible exception of the nicotine inhalator, neither do they replace the sensory and behavioural cues associated with cigarette use. Indeed, many smokers find available NRTs unhelpful, unpleasant or difficult to use and want more product choice [5].

Electronic nicotine delivery systems (ENDS), more commonly known as electronic cigarettes (hereafter abbreviated to 'e-cigarettes' or 'e-cigs'), are so-called because of their physical resemblance to a standard tobacco cigarette and their electronic vapour-generating mechanism. In 2004 a Beijing-based company, Ruyan Group (Holdings) Ltd, patented and launched the first of these devices [6]. Many other manufacturers have since made similar devices. All contain a mouthpiece, a micro-electrical circuit, a vaporiser, and a rechargeable lithium ion battery. The solution in replaceable cartridges or used to fill a reservoir in some models typically contains a solution of humectants (e.g. propylene glycol and/or glycerol), and nicotine and flavourings. When a user draws air through the e-cigarette the micro-electrical circuit activates an electric coil to heat and vaporise a small amount of the nicotine solution, creating a visible cloud of mist that may be inhaled by the user [7].

It has been hypothesised that e-cigarettes could be more effective than NRT at helping people quit smoking by delivering nicotine together with mimicking the physical, sensory and behavioural aspects of cigarette use [1,8]. In international online surveys one of the key reasons people report buying e-cigarettes is to help quit smoking [9,10].

In 2008 we undertook the first study of the effect of the e-cigarettes on desire to smoke and withdrawal symptoms and found that they were as effective as the NRT inhaler on reducing withdrawal but more pleasant and acceptable to use [8]. Further research has generally supported these early findings, and none to date have found evidence of harm [6]. We also found that the speed of nicotine delivery and serum levels obtained was substantially less than tobacco cigarettes. This has been corroborated with other brands by other research groups [11,12].

A related question is the extent to which any quitting assistance provided by e-cigarettes might be attributable simply to the behavioural replacement they provide, as suggested by a study of a nicotine-free inhaler device by Capponeto et al. [13]. This is relevant to countries such as New Zealand where e-cigarettes are available for sale over the counter but without cartridges containing nicotine.

E-cigarette sales are increasing rapidly: in the US alone there are an estimated 2.5 million users with sales of $300 million a year [14]. Internet search volumes have surpassed search volumes for both NRT and varenicline in the UK, US and Canada [15]. Despite this evidence of consumer demand, there are mixed views in the tobacco control community as to what role, if any, e-cigarettes might play in helping smokers to cease tobacco use. Strong concerns have been expressed over their potential to be a gateway to tobacco smoking, the safety of the inhaled vapours and ability of the devices to deliver nicotine as claimed [16-18].

Although a few studies have been conducted that show promise for the potential of e-cigarettes as cessation aids [19-21], none have been adequately powered. As noted, a number of surveys of users suggest potential in this area, but to date, no randomised trials that evaluate the long- term efficacy e-cigarettes on abstinence, in smokers motivated to quit, have been completed. Nor has there been a systematic evaluation of their safety. A well-designed trial is urgently needed to inform policy development on the regulation and availability of these and the many other emerging nicotine cigarette substitute products [22,23].

## Aim

The primary aim of the trial is to assess the effectiveness, acceptability, patterns of use and safety of e-cigarettes as a smoking cessation aid. The study will determine the quit rates of smokers using nicotine versus nicotine patch and versus placebo (non-nicotine) e-cigarettes at six months. The trial hypotheses are:

• nicotine e-cigarettes are more effective than nicotine patches on smoking abstinence at six months;

• nicotine e-cigarettes are more effective than placebo e-cigarettes on smoking abstinence at six months;

• nicotine e-cigarettes are more effective than placebo e-cigarettes at relieving withdrawal symptoms and suppressing cravings to smoke;

• e-cigarettes are safe to use over a 13 week period;

• e-cigarettes are an acceptable treatment for smokers trying to quit.

## Methods/design

### Design

A three-arm, parallel-group randomised controlled trial.

### Study population

People from throughout Auckland, New Zealand, who smoke tobacco cigarettes and are motivated to quit.

### Inclusion and exclusion criteria

Participants will be eligible provided they are at least 18 years of age, have smoked at least 10 cigarettes a day for the past year, want to stop smoking, are able to provide verbal consent and have access to a telephone. Pregnant and breastfeeding women will be excluded, as will be people using other smoking cessation medications (including other forms of NRT, bupropion, clonidine, nortriptyline or varenicline) or who are clients of a smoking cessation programme or enrolled in another trial. People will be excluded if they report having had a heart attack, stroke or severe angina in the previous two weeks; poorly controlled asthma or other airways disease from self-report; poorly controlled diabetes mellitus; severe allergies; poorly controlled psychiatric disorders or current chemical dependence other than that involving nicotine.

### Recruitment

People resident in the Auckland region will be informed of the trial through short articles about the study in free weekly community newspapers and targeted television programming to patients waiting to see their doctor in the waiting rooms of community general practices. People interested in enrolling will be invited to contact the study centre at the University of Auckland’s National Institute for Health Innovation (NIHI) by free telephone to obtain further information, complete informed consent and undergo eligibility pre-screening. We hope to recruit as many Māori (indigenous New Zealanders) as possible to be able to test any effect of the intervention on Māori compared with non-Māori participants, because 40% of Māori smoke tobacco and have a high burden of smoking-related illness.

### Randomisation, allocation concealment and sequence generation

Callers will be told about the trial and asked if they would like to take part by a research assistant. If interested, they will be asked for basic demographic data (age, sex and ethnicity) and checked to see if they meet the trial inclusion criteria. Those who provide further details about their level of nicotine dependence (determined by the Fagerström Test for Nicotine Dependence [FTND] questionnaire [24]) will be randomised by a central computer programme to one of the three study groups using stratified block randomisation with block sizes of nine. The randomisation sequence will be prepared in advance by the study statistician (VP) but will be concealed from research assistants enrolling participants. Participants will be assigned to the 16 mg e-cigarette and nicotine patch groups in a ratio of 1:1 (290 in each) and to the nicotine e-cigarette and placebo e-cigarette groups in a ratio of 4:1 (73 in the latter arm). Three stratification factors will be used: ethnicity (Māori, Pacific, non-Māori non-Pacific), sex (male/female) and level of nicotine dependence (> 5 or ≤ 5 on the FTND [24]).

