### Blinding

Due to the nature of the treatment it is not possible to blind participants to the use of e-cigarettes or nicotine patch. However, participants will be blind to the allocation of nicotine or placebo e-cigarettes as there is no difference in appearance or odour of the mist emitted from the 16 mg/ml nicotine and 0 mg/ml nicotine cartridges, nor do they differ in physical appearance. Members of the trial steering committee, management committee, and other team members (with the exception of the project co-ordinator and research assistants) will remain blind to treatment allocation until the code is broken after the last follow-up call is completed and the data recorded. The project co-ordinator and research assistants are not blinded as they are responsible for distributing the treatment to participants. To minimise the risk of bias, strict protocols for follow-up assessment procedures will be developed and the research assistants trained in adhering to these.

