### Study interventions

Participants will be randomly allocated to Elusion™ e-cigarettes supplied by PGM International with nicotine cartridges (16 mg), to nicotine patch (Habitrol^®^ 21 mg patch, distributed in NZ by Novartis Consumer Health Australasia Pty. Ltd.) or to e-cigarettes with placebo (0 mg) cartridges in a ratio of 4:4:1. Participants issued with an e-cigarette will be instructed to charge the batteries daily for reliable operation using a USB charger that comes with the device, alone or in combination (if needed) with an adaptor plug.

Participants in the 16 mg nicotine e-cigarette treatment arm will be sent (by courier) a free e-cigarette and sufficient nicotine cartridges (16 mg/ml) to last for four to five weeks. Participants will be instructed to use the device *ad libitum* one week before their quit day to familiarise themselves with its operation and on their designated quit day will stop smoking tobacco cigarettes and instead use the e-cigarette exclusively for the next 12 weeks.

Those in the placebo e-cigarette arm will be sent a free e-cigarette and cartridges containing 0 mg nicotine. Participants will use the device in the same manner as described above for the nicotine e-cigarette treatment group. The cartridges will be labelled in such a way that participants cannot detect if they contain nicotine.

In the nicotine patch arm, participants will be sent (by post) vouchers to be exchanged for a minimal dispensing fee (NZ$3) at any community pharmacy for 21 mg (full strength, 24 hour) nicotine patches. All participants will receive a $5 voucher to be used at any community pharmacy on any product they wish, to cover their out of pocket expenses. Participants will use the nicotine patch daily for one week before their quit day to familiarise themselves with its use. On their designated quit day they will stop smoking and use nicotine patches daily for the next 12 weeks. This dosing regimen is consistent with what is now regarded as standard treatment in NZ and many other countries. The 21 mg strength patch is likely to be sufficient nicotine replacement for the majority of smokers recruited into the trial.

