### Sample size

A sample size of 657 people (292 in both nicotine-cigarette and nicotine patch groups and 73 in the placebo e-cigarette group) will provide 80% power at a two-sided p = 0.05 to detect an absolute difference of 10% in smoking abstinence rates between the nicotine e-cigarette and patch groups, and a difference of 15% between the nicotine and placebo e-cigarette groups. This assumes quit rates of 15% in the placebo e-cigarette group and 20% in the nicotine patch group (based on meta-analyses of NRT trials by Fiore et al. [29] and our own trials of nicotine patch [30]). This sample size allows for analysis of consistency of effects for pre-specified subgroups (e.g. Maori, non-Maori) to be assessed. Based on our previous experience we estimate recruitment will take approximately 12–15 months [31].

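### A single fixed block size of nine, with unblinded enrolling staff, could let up to about 15–16% of allocations be deduced if staff know the block size and keep count by stratum

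*Protocol article*

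**What the plan says.** The section on randomisation, allocation concealment and sequence generation has a central computer programme allocate participants "using stratified block randomisation with block sizes of nine". No other block length is mentioned. The section adds: "Three stratification factors will be used: ethnicity (Māori, Pacific, non-Māori non-Pacific), sex (male/female) and level of nicotine dependence". These factors are collected before the computer allocates. The sequence is prepared in advance by the study statistician and "will be concealed from research assistants enrolling participants". First contact is also with a research assistant: "Callers will be told about the trial and asked if they would like to take part by a research assistant".

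The Study interventions section gives the ratio, with participants allocated to nicotine e-cigarettes, to patch or "to e-cigarettes with placebo (0 mg) cartridges in a ratio of 4:4:1".

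The Blinding section states: "The project co-ordinator and research assistants are not blinded as they are responsible for distributing the treatment to participants". The safeguard offered there, strict procedures and training, concerns follow-up assessment and not enrolment.

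**The concern.** Concealing the list protects enrolment only if the next allocation cannot be worked out from earlier ones. A block of nine at 4:4:1 always holds four nicotine e-cigarettes, four patches and one placebo e-cigarette. Someone who knows this and has seen the earlier allocations in the stratum can sometimes name the next arm with certainty. Here the role that screens and enrols callers is also the role that sees allocations, and the stratum is known before randomisation.

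What is at stake is selection bias in the comparison of e-cigarette with patch, to which participants cannot be blinded. Several eligibility criteria are judged by telephone, such as wanting to stop smoking or having a condition that is poorly controlled. A staff member who foresees the next arm could encourage or delay a caller, even without meaning to. If the callers affected differ in motivation or dependence, abstinence at six months could differ between arms for reasons other than treatment.

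**Working it through.** **The plan's own figures.** The article gives no predictability figure. Its sample size fits the block design: 292 + 292 + 73 = 657, and 657 / 9 = 73 blocks, each with 4 + 4 + 1. I use 657 from the Sample size section.

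**Inputs**
- Block of nine, single size (randomisation section).
- Contents 4 nicotine e-cigarette, 4 patch, 1 placebo e-cigarette (Study interventions).
- Strata: 3 ethnicity groups × 2 sexes × 2 dependence levels = 12 (randomisation section).
- Assumption, not in the article: staff know or infer the block size and pool all past allocations by stratum.

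**Complete blocks, three arms.** An allocation is certain when all slots left in its block belong to one arm. The expected number per block is the sum over k of P(last k slots all the same arm):

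| k | Block position | Probability |
|---|---|---|
| 1 | 9th | 1 |
| 2 | 8th | 2 × (4×3)/(9×8) = 1/3 |
| 3 | 7th | 2 × (4×3×2)/(9×8×7) = 2/21 |
| 4 | 6th | 2 × (4×3×2×1)/(9×8×7×6) = 1/63 |

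Sum = 1 + 1/3 + 2/21 + 1/63 = 13/9 per block. As a share, (13/9)/9 = 13/81 = 16.0%. Over the trial, 73 × 13/9 ≈ 105 of 657.

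**Complete blocks, e-cigarette (either kind) versus patch.** The contents are 5:4:
- k = 2: (5×4 + 4×3)/72 = 4/9
- k = 3: (60 + 24)/504 = 1/6
- k = 4: (120 + 24)/3024 = 1/21
- k = 5: 120/15120 = 1/126

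Sum = 1 + 4/9 + 1/6 + 1/21 + 1/126 = 5/3 per block. As a share, (5/3)/9 = 5/27 = 18.5%.

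**Incomplete final blocks.** With 657 people spread over 12 strata, simulation (1,000 trials per setting) leaves about 10 to 11 blocks unfinished. Certain allocations average 98.5 (15.0%) with equal strata and 98.7 (15.0%) with an assumed skewed mix. For e-cigarette versus patch the average is about 114 (17.3%) in both settings.

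**Best guess.** Naming the arm with most slots left is right 60.4% of the time over a complete block, against 4/9 = 44.4% without tracking.

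**Alternatives under the same assumption**
- Fixed blocks of 18 (8:8:2): 49/561 = 8.7% certain in complete blocks.
- Lengths of 9 or 18 chosen at random, staff knowing both possible sizes but not the current one: about 25.6 of 657 (3.9%) certain, from 300 simulated trials with equal strata. The same program with fixed blocks of nine gave 97.8 (14.9%), in line with the result above.

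**The case against.** The strongest case against is that the decisive premise is absent from the article. Certain prediction needs staff to know the block size and to keep a complete count in each of 12 strata. The article describes a central computer and a concealed list, and a condensed article may leave the withholding of block size to the full protocol. Fixed blocks with central allocation are a recognised design. This stands: the percentages are upper bounds under an assumption.

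A reader might infer more: that one allocation in six is in fact foreseeable, that each enroller sees every allocation, or that concealment has failed. The text supports none of these. It says only that the co-ordinator and research assistants, as a group, are unblinded. It does not say that a tally by stratum is visible, or that the same individuals enrol and dispatch.

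It can also be said that the remedy relies on secrecy while secrecy is denied to the present design. That is only partly right. The 3.9% figure already grants staff knowledge of the two possible sizes and needs only the current one to be unknown. Nine is also the smallest block that fits 4:4:1, so it is easy to guess. Equally, varied lengths do not remove certainty: once the first nine depart from 4:4:1, a tracker knows that the block is 18.

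The route to bias is uncertain as well. Callers refer themselves, dependence is established late in the call, and nothing shows that staff would favour an arm. The Background suggests that many smokers dislike existing nicotine replacement products, but that is not a staff motive. The planned adjusted logistic regression could address measured imbalance, though not unmeasured. These points lower the likely size of any bias. None of them is a safeguard at enrolment.

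**Conclusion.** The weakness is real but conditional. One fixed block size, strata known before randomisation and unblinded staff in the enrolling role mean that hiding the list does not by itself prevent the ends of blocks from being deduced. If staff know or infer the block size and tally by stratum, up to about 15–16% of allocations could be known with certainty (about 98 of 657 allowing for incomplete final blocks, 105 if all are complete). For e-cigarette versus patch the figure is about 17 to 18.5%. This can weaken the stated concealment; it is not shown to defeat it, and no bias in a given direction is demonstrated. The point is worth acting on because the remedy is cheap and no stated measure protects enrolment.

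**What to change.** For all blocks not yet opened, the statistician should generate the list with lengths of 9 and 18 in random order within each stratum. This keeps 4:4:1. The lengths should be withheld from enrolling staff. Under the assumptions above, certain predictions fall from about 15% to about 4% (about 26 of 657).

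The cost is slightly more imbalance from incomplete blocks at the end of recruitment, and a controlled change to a live randomisation list. Timing limits what can be done: recruitment began in August 2011 and was expected to take 12–15 months, so few or no unopened blocks may remain.

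If none remain, the trial report should state that the block size was fixed at nine, whether it was withheld from enrolling staff, and whether those who enrolled participants also dispatched treatment. That costs a few sentences and lets readers judge the risk.

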### Blinding

Due to the nature of the treatment it is not possible to blind participants to the use of e-cigarettes or nicotine patch. However, participants will be blind to the allocation of nicotine or placebo e-cigarettes as there is no difference in appearance or odour of the mist emitted from the 16 mg/ml nicotine and 0 mg/ml nicotine cartridges, nor do they differ in physical appearance. Members of the trial steering committee, management committee, and other team members (with the exception of the project co-ordinator and research assistants) will remain blind to treatment allocation until the code is broken after the last follow-up call is completed and the data recorded. The project co-ordinator and research assistants are not blinded as they are responsible for distributing the treatment to participants. To minimise the risk of bias, strict protocols for follow-up assessment procedures will be developed and the research assistants trained in adhering to these.

